Altered patterns of synaptic plasticity have also been identified in the setting of bipolar disorder, bearing implications for interventions that modulate synaptic plasticity [38]. Animal models have demonstrated that ketone bodies are capable of stimulating brain-derived neurotrophic factor (BDNF) production [39,40], converging with evidence in human research [41,42,43]. BDNF is widely known as a vital modulator of synaptic plasticity.

Looking beyond the level of the synapse, a growing body of functional neuroimaging research has revealed that bipolar disorder is characterized by abnormalities in neural network functional connectivity. In particular, altered interactions between the amygdala and prefrontal regions have been implicated in bipolar disorder [44]. Via an elegant fMRI analysis, Mujica-Parody et al. [45] found that the ketogenic diet has a stabilizing effect on neural network functional connectivity. Moreover, exogenous ketone esters also demonstrated a stabilizing effect on neural network functional connectivity, even if consumed in the setting of a regular diet. Theoretically, the stabilization of neural networks may also bear implications for the management of bipolar disorder. This line of reasoning would be consistent with patterns of altered neuronal excitability identified in the setting of bipolar disorder [46], as altered patterns of spreading activation would be an expected downstream effect of altered neuronal excitability.

Furthermore, with a growing body of evidence demonstrating intersections between neuroinflammatory processes and psychiatric disorders, it is plausible that the anti-inflammatory properties of ketone bodies may prove to be therapeutic for patients suffering from bipolar disorder [47,48,49]. Neuroinflammatory processes have been implicated in the pathogenesis of the bipolar disorder, as demonstrated via markers of excitotoxicity and neuroinflammation mediated by the IL-R cascade [50]. Ketone bodies have been shown to inhibit activation of the NF-κB inflammasome (a key orchestrator of this signaling cascade) [51,52].

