### 3.3. Outcome Measures

Primary outcome measure:Neural network stability as ascertained via functional magnetic resonance imaging (fMRI)

Secondary outcome measures:Neural uptake of ketone bodies as ascertained via magnetic resonance spectroscopy (MRS)Clinical assessments and global functioning metrics (see Table 1)Laboratory assessments (see Table 2)Continuous glucose monitoring (CGM) glycemic trendsß-hydroxybutyrate (ß-HB) blood level (as ascertained via Keto-Mojo™ monitoring device)Sleep quality (as ascertained via Oura™ biometric ring)

Primary Aim: To compare fMRI neural network stability before and after a low glycemic index dietary intervention combined with open-label supplementation of exogenous ketones, namely bis hexanoyl (R)-1,3-butanediol (available over the counter as an athletic performance and health supplement called Juvenescence ‘Metabolic Switch^®^’ powder and also referred to as ‘C6 ketone di-ester’) in a biomechanistic pilot study in individuals with bipolar disorder (*n* = 34 [please see Supplementary Materials for sample size calculation]). While a comprehensive low glycemic index diet may also be considered to augment the effects of exogenous ketone supplementation, for simplicity and ease of adherence the low glycemic index intervention in this protocol will be comprised of four simple dietary changes as follows:Not consuming soda for the duration of the intervention period.Not consuming candy/sweets for the duration of the intervention period.Not consuming white grains/rice for the duration of the intervention period, instead replacing these with complex carbohydrates such as whole grains and brown rice.If consuming fruit with a meal, eating the fruit at the end of the meal to minimize glycemic spiking.

Timetable: This study, to be completed over a 3-year period, will include a net total of *n* = 34 subjects with bipolar disorder. Details of the enrollment and major test procedures are outlined in Table 3. Milestone of recruitment success is net completion of 24 persons by the end of year 2. A gross total of up to 50 subjects will be recruited to account for possible attrition.

Design: Exploratory pilot study assessing open-label ketone ester supplementation (19 g BID PO; 12.5 g active ingredient per serving) in combination with low glycemic index dietary intervention.

Inclusion criteria

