To be eligible for the study, an individual must meet the following criteria:Adults 18 and older, able to provide informed consentDiagnosis of bipolar disorder (any subtype)

Exclusion criteria

An individual who meets any of the following criteria will be excluded from participation in the study:History of traumatic brain injuryEvidence of large vessel stroke or mass lesion on MRIHistory of significant gastrointestinal disease or malabsorptive disorderPregnancy or breastfeedingUncontrolled diabetes mellitusHistory of mitochondrial disorder and/or significant uncontrolled metabolic/medical disorderActive/current substance dependence (and/or consumption of two or more alcoholic beverages per day)Subjects with contra-indications to MR imaging, including pacemakers or severe claustrophobiaActive suicidal or homicidal ideation

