
**Table 3 nutrients-15-03068-t003:** Study Overview.

Outcome Metric	Pre-Intervention Imaging *	Baseline Clinical Assessment *	Daily	Mid-Intervention	Post-Intervention Imaging *	Post-Intervention Clinical Assessment *
fMRI/MRS	X				X	
CGM	X	X			X	X
Oura™	X	X	X	X	X	X
YMRS		X		X		X
BDI		X		X		X
PHQ-9		X		X		X
Mood Surveys		X	X	X		X
CGI		X		X		X
GAF		X		X		X
LFQ		X		X		X
SDS		X		X		X
STAI		X		X		X
SF-36		X		X		X
Blood ketones		X		X		X
Blood glucose		X		X		X
Lab assays (see Table 2)		X				X

* For visits 1–2 and 4–5: There is no pre-set sequence for which assessment (clinical or imaging) comes first.

**Hypothesis 1**.
*Neural network stability in subjects with bipolar disorder will improve after the approximately 90-day intervention involving supplementation with 19 g BID PO of ketone ester (containing 12.5 g C6 ketone di-ester per serving).*

**Hypothesis 2**.
*Greater neural uptake of ketone bodies as measured via MRS will correlate with greater improvement in neural network stability.*

**Hypothesis 3**.
*Greater glucose lability (glucose spikes demonstrated via CGM trends) will correlate with less favorable response to the intervention.*

**Hypothesis 4**.
*Lower Glucose Ketone Index (GKI) (as measured via Keto-Mojo™ device) will correlate with more favorable response to the intervention.*

Exploratory Hypothesis 1: Neural network instability as ascertained via fMRI may correlate with mood instability as ascertained via self-reported mood surveys.

Exploratory Hypothesis 2: Ketone ester supplementation combined with low glycemic index dietary changes may correlate with improved metabolic biomarkers (e.g., hs-CRP or serum lactate).

Exploratory Hypothesis 3: Greater neural uptake of ketone bodies as measured via MRS and greater increases in blood ketone level as measured via Keto-Mojo™ device may correlate with greater improvements in mood stability and global functioning.

Impact: Positive findings in this small exploratory pilot study may support future target engagement studies of ketone ester supplementation or other ketogenic interventions in bipolar disorder.

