## 6. Limitations

A number of limitations must be recognized for this research protocol. Importantly, this pilot study protocol does not feature a control group for feasibility and budgetary purposes. While the biasing of outcomes via potential placebo effects can be mitigated to some extent by focusing on objective biomarker outcomes, this methodology nonetheless introduces confounders that will undoubtedly need to be addressed in subsequent studies. Another key consideration for this protocol is the challenge of adherence to a dietary intervention. While adherence to the intervention will be assessed via self-report (through both regular check-ins with study coordinators and daily consumption logs), glucose level trends (ascertained via CGM data), ketone level trends (ascertained via Keto-Mojo™ data), and supplement accountability (including study coordinators measuring how much ketone ester supplement has been exhausted from containers at study completion), it must be noted that each of these adherence measures has limitations and imperfections. Finally, the authors anticipate that the effect size associated with a ‘ketogenic-mimicking diet’ will be moderate relative to the strong effect sizes reported with strict ketogenic diets. With no preexisting clinical studies investigating ketone ester supplementation combined with low glycemic index dietary changes in the setting of bipolar disorder, some educated assumptions are inherently necessary when predicting statistical power and minimum sample size. This suggests the possibility that a small pilot study may be underpowered given the uncertain magnitude of biomechanistic effects.

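### The printed eligibility criteria admit people already on a ketogenic diet or already taking exogenous ketones, which shrinks the before/after contrast that is this single-arm study's only comparison

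*Protocol article*

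**What the plan says.** Section 3.3 of the protocol article lists two inclusion criteria (a consenting adult; bipolar disorder of any subtype) and nine exclusions under the sentence "An individual who meets any of the following criteria will be excluded from participation in the study". The exclusions cover neurological, gastrointestinal, metabolic, obstetric, substance-use, MR-safety and acute-risk conditions. Current diet, ketosis and ketone supplements do not appear, and the article states no washout or run-in.

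The same section describes the supplement as "available over the counter as an athletic performance and health supplement". The primary aim is "To compare fMRI neural network stability before and after a low glycemic index dietary intervention combined with open-label supplementation of exogenous ketones". Section 6 says that "this pilot study protocol does not feature a control group for feasibility and budgetary purposes".

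Section 2 credits the ketogenic diet with a stabilising effect on network connectivity and adds that "exogenous ketone esters also demonstrated a stabilizing effect on neural network functional connectivity, even if consumed in the setting of a regular diet".

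The study procedures collect about a week of continuous glucose monitoring (CGM) before the intervention and a day-0 ketone and glucose reading. Neither is tied to eligibility. Hypothesis 4 predicts that a lower GKI "will correlate with more favorable response to the intervention", without saying whether GKI is a baseline level, an on-treatment level or a change.

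**The concern.** With one arm, the baseline scan is the only comparator. If the rationale in Section 2 is right, someone who arrives in ketosis or already taking ketone ester has a baseline scan that is already shifted on the primary outcome. Their measured change will then understate what the intervention does in an unexposed person.

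The bias for Hypothesis 1 runs toward no effect, and the Abstract gives a null result a specific use: it may support turning to stricter diets in later research. Participants who were already on a strict diet would help to produce that null for a reason unrelated to the intervention. The adherence checks in Section 6 (logs, glucose and ketone trends, supplement accounting) would not expose the problem, because such people would look highly adherent. Section 6 does not list prior exposure among the limitations.

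**Working it through.** **Who loses how much contrast.** Everyone starts the ester, and Hypothesis 1 is worded on the ester.

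- Already on comparable ester and already following all four Table 4 changes: no contrast.
- On a ketogenic diet without ester: contrast reduced by an unknown amount.
- Low-glycemic eating only: the dietary part of the contrast is reduced, but the ester part remains, since Section 2 expects an ester effect even on an ordinary diet.

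**The plan's own figure.** The article gives a net n of 34 and refers the calculation to the Supplementary Materials, which are not shown. It gives no alpha, power or standardised effect, so 34 cannot be reproduced from its inputs. As a conditional check, take a paired t-test, d = 0.5, two-sided 5% and 80% power. The noncentrality is 0.5 × √34 = 2.92 on 33 degrees of freedom, power is 80.8%, and the smallest n reaching 80% is 34. Other input sets land nearby (d = 0.6, two-sided, 90% power gives 32; d = 0.5, one-sided, 90% power gives 36), so the agreement does not identify the authors' inputs.

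**Dilution for Hypothesis 1.** Let a share f keep a fraction r of the mean change, with a within-group SD of 1:

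- mean = 0.5 × [(1 − f) + f r]
- SD = √[1 + 0.25 f (1 − f)(1 − r)²]
- diluted d = mean / SD, put into the same t-test at n = 34

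Example, f = 10% and r = 0: mean 0.45, SD √1.0225 = 1.011, d = 0.445.

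| Exposed share f (assumed) | Contrast kept r | d | Power at n = 34 | n for 80% |
|---|---|---|---|---|
| 0 | – | 0.50 | 80.8% | 34 |
| 5% | none | 0.472 | 76% | 38 |
| 5% | half | 0.487 | 79% | 36 |
| 10% | none | 0.445 | 71% | 42 |
| 10% | half | 0.474 | 76% | 37 |
| 20% | none | 0.392 | 60% | 53 |
| 20% | half | 0.448 | 72% | 42 |

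**Hypothesis 4 (illustrative simulation, 400,000 draws).** In unexposed people, response correlates −0.30 with on-treatment GKI. Exposed people have GKI 1 to 2 SD lower and a mean change of zero. Correlation of GKI with response:

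| GKI used as | f = 0 | f = 10% | f = 20% |
|---|---|---|---|
| On-treatment level | −0.30 | −0.22 to −0.16 | −0.15 to −0.06 |
| Baseline level | −0.21 | 0.00 to +0.03 | +0.08 to +0.11 |
| Change | −0.21 | −0.25 | −0.27 |

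An on-treatment level weakens the expected association, a baseline level can reverse its sign, and a change score strengthens it. When the true association is set to zero, the change score still gives about −0.10 at f = 10% and −0.15 at f = 20%. That would be spurious support for the hypothesis.

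**The case against.** The strongest reply is that few enrolled people may be exposed and most of those would keep some contrast. This stands. A reader might infer that anyone already eating a ketogenic or low-glycemic diet has no before/after contrast. The documents do not support that, because the ester is new to most such people and is expected to act without a diet change.

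A reader might also infer that current users are the likeliest volunteers, since Section 2 cites online forum reports of ketogenic diets in bipolar disorder. Those reports show that such users exist. They say nothing about this trial's recruits or about ester use.

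A third tempting reading is that Hypothesis 4 is necessarily pushed the wrong way. That depends on a GKI definition the article does not give.

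It can also be said that the baseline CGM and ketone data could flag many exposed people for adjustment or a sensitivity analysis, and that an analysis plan not shown may do so. That is fair, but adjustment cannot supply the missing unexposed scan. A fuller protocol might contain further criteria, yet the article prints these lists as the ones that decide entry. Finally, this is an exploratory pilot, the bias on Hypothesis 1 is conservative, and Section 6 already concedes that power may be low. All of that limits the severity. It does not remove a gap that one line can close.

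**Conclusion.** The point holds in a limited form. As printed, the criteria can admit people whose baseline is already shifted on the primary outcome, and in an uncontrolled before/after design this biases Hypothesis 1 toward no effect. The direction follows from the article's own rationale. The size does not, because the exposed share and the contrast such people keep are both assumptions. On an assumed d of 0.5 (the article says only that the effect should be moderate compared with strict ketogenic diets), the loss is about 4 to 10 percentage points of power at 10% exposed and 9 to 20 points at 20%. The lower power figures in each range are the zero-contrast extreme, which applies only to people already on comparable ester and all four dietary changes.

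For Hypothesis 4 the expected association is weakened with an on-treatment GKI, can change sign with a baseline GKI, and is not weakened with a change in GKI. Nothing here shows that n = 34 is wrong.

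**What to change.** Add one exclusion: a current ketogenic diet, or use of exogenous ketone supplements, within a fixed period before the first baseline visit, with the period set by the study team. Check it with a screening question.

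If a ketone reading is used as well, take it at screening, before the baseline scan. The scheduled day-0 reading is not a clean screen: the Table 3 footnote lets imaging or clinical assessment come first, so that reading may follow the scan.

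Record habitual intake of the Table 4 items at baseline, and use it with the baseline CGM and ketone data in a prespecified sensitivity analysis. Do not make regular intake of a restricted food an entry requirement, since that would narrow a study meant to test an accessible intervention. State which GKI (time point, and level or change) Hypothesis 4 uses.

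The cost is one eligibility line, a short screening question, possibly one extra ketone reading, a few lost volunteers and slightly slower recruitment. The margin between 50 recruited and 34 completing (16 people) is set aside for attrition, so it should not be assumed to cover screen failures too.

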Study procedures and assessments: After obtaining informed consent and screening for study eligibility, study participants will undergo the baseline clinical assessment and imaging protocol (separate days). There will be a total of 5 visits for this pilot study. The baseline clinical assessment will include standardized assessments of global functioning and symptom severity (summarized in Table 1). Participants will also be instructed to wear a continuous glucose monitor (CGM) and a biometric device called Oura™ ring for 7 (±3) days prior to starting the intervention, allowing for assessment of baseline glycemic trends as well as sleep and activity data. They will also have their blood drawn for laboratory assessments at the pre-intervention clinical visit (assays detailed in Table 2)—blood-derived laboratory assays will be optional for participants (e.g., to accommodate participants with a strong preference to avoid blood draws or a specific phobia pertaining to blood). Upon completion of this baseline assessment, participants will initiate the 90 (±10)-day intervention (ketone ester supplementation in combination with low glycemic index dietary changes). During the intervention period, participants will be prompted to submit daily ratings of mood via the CareEvolution platform. They will also be instructed to check their blood ketone/glucose levels using a Keto-Mojo™ ketone/glucose monitor on intervention days 0 (baseline), 45 (±10) (mid-intervention), and 90 (±10) (post-intervention): measurements will be taken before supplementation (morning fasting) and two hours post-supplementation. At the mid-intervention point (day 45 ± 10 days), participants will repeat the comprehensive neurobehavioral assessment summarized in Table 1. At the end of the intervention period, they will repeat a 7–10 day CGM assessment. After completing the intervention, participants will repeat the clinical/laboratory assessments and imaging protocol (on separate days). They will continue to wear their Oura™ ring throughout the intervention period and for a 14 (±7)-day post-intervention follow-up period. Daily mood ratings will also be continued during this post-intervention follow-up period until the Oura™ wearable is returned, at which point study participation will be completed. For a visual overview of this study design, please refer to the schedule of events outlined in Table 3 and the flowchart depicted in Figure 1. A visual overview of key outcome metrics is featured in Figure 2.

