**Figure 5 nutrients-15-03068-f005:**
[figure not shown]
Metabolic Dysfunction in Context: Biopsychosocial Model. Importantly, metabolic dysregulation should be conceptualized within the broader context of the biopsychosocial model. There are many upstream and downstream factors integrated with metabolism, including lifestyle factors (such as nutrition, exercise, and sleep), medical comorbidities, medications, substance use, trauma, and chronic stress. Accumulating evidence supports the critical role of mitochondrial function in bipolar illness, which may help explain how altered neuronal excitability represents just one component of a broader model connecting biological and metabolic mechanisms with psychological and social risk factors [60]. As a pertinent example, stress and trauma have been linked to alterations in cortisol signaling and mitochondrial function [61]. Moreover, this figure illustrates a critical link between altered neuronal excitability and altered patterns of neural network functional connectivity, as patterns of spreading activation throughout neural networks are inherently dependent on patterns of neuronal excitability. The foundation of the image depicts how these mechanisms may ultimately culminate in suffering experienced by the patients we serve—something that should not be overlooked for the sake of mechanistic granularity.

**Table 1 nutrients-15-03068-t001:** Neurobehavioral survey battery.

Clinical Outcome	Metric
Mania Symptomatology	Young Mania Rating Scale (YMRS)
Depression Symptomatology	Beck Depression Inventory (BDI) Patient Health Questionnaire-9 (PHQ-9)
Mood Stability	Brief daily mood surveys delivered via CareEvolution platform
Global Functioning	Clinical Global Impression (CGI) Global Assessment of Functioning (GAF) Life Functioning Questionnaire (LFQ) Sheehan Disability Scale (SDS)
State and Trait Anxiety	Spielberger State-Trait Anxiety Inventory (STAI)
Quality of Life	36-Item Short Form Health Survey (SF-36)

**Table 2 nutrients-15-03068-t002:** Laboratory assessments *.

High-sensitivity C-reactive protein (hs-CRP)
Comprehensive metabolic panel (CMP)
Peripheral mitochondrial function assessment (e.g., serum lactate, WBC mitochondrial DNA copy number, mitochondrial haplotype, or Seahorse assay)
Urine drug screen (UDS)

* Lithium level monitoring may be considered for participants taking lithium due to theoretical interaction effects in the setting of ketone metabolism.

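### No pre-intervention series of daily mood ratings is stated, so change from baseline in mood stability has no untreated reference

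*Protocol article*

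**What the plan says.** All references are to the protocol article.

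- **Metric.** Table 1 gives mood stability one instrument: "Brief daily mood surveys delivered via CareEvolution platform".
- **Start and end.** The study procedures paragraph of Section 3.3 states: "During the intervention period, participants will be prompted to submit daily ratings of mood via the CareEvolution platform". It then extends the ratings past treatment: "Daily mood ratings will also be continued during this post-intervention follow-up period until the Oura™ wearable is returned". The follow-up lasts 14 (±7) days.
- **Run-in.** Before treatment, participants are to "wear a continuous glucose monitor (CGM) and a biometric device called Oura™ ring for 7 (±3) days prior to starting the intervention". The stated purpose is a baseline for glucose, sleep and activity. Mood is not named.
- **Baseline visit.** "The baseline clinical assessment will include standardized assessments of global functioning and symptom severity (summarized in Table 1"), and Table 1 includes the daily survey.
- **Schedule.** The Table 3 row reads "Mood Surveys X X X X". The marks fall under baseline clinical assessment, Daily, mid-intervention and post-intervention clinical assessment. The Daily column carries no dates.
- **Use.** Exploratory Hypothesis 3 relates ketone uptake and blood ketone increases to "greater improvements in mood stability and global functioning". Exploratory Hypothesis 1 relates fMRI network instability to self-reported mood instability. Section 4 plans exploratory regressions of pre/post differences in a range of mood, functioning and laboratory measures.

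**The concern.** Stability describes how much a person's ratings move from day to day, so it needs a series of ratings. An improvement in stability needs two such series, one of them before treatment. The article provides this for glucose and sleep by having the devices worn ahead of the intervention, but states no equivalent for mood.

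Section 6 acknowledges that there is no control group, so each participant's untreated period is the only reference for change. If daily ratings begin with the supplement, that reference is missing for mood stability. The pre-intervention scan likewise has no daily mood data from the same period. No analysis plan can recover ratings that were never collected.

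**Working it through.** The plan gives no figure that depends on this point, so there is nothing to reproduce. The check has two parts.

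**1. Which periods have a stated daily series**

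| Period | Glucose monitor | Ring | Daily mood survey |
|---|---|---|---|
| Run-in, 7 (±3) days | Stated in text | Stated in text | Not stated; one mark at the baseline visit in Table 3 |
| Intervention, 90 (±10) days | Repeated for 7–10 days at the end | Stated | Stated |
| Follow-up, 14 (±7) days | Not stated | Stated | Stated |

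Mood stability is the only one of the three with no stated daily series before treatment.

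**2. What a given number of baseline ratings can support**

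Inputs: the run-in spans 7 − 3 = 4 to 7 + 3 = 10 days, and the intervention about 90 days (both Section 3.3). The article does not define the stability statistic. I assume a within-person SD from k independent, normal daily ratings.

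- Degrees of freedom: k − 1.
- Approximate relative standard error of the SD: 1/√(2(k − 1)).
- 95% interval, as multipliers of the observed SD: √((k − 1)/χ²₀.₉₇₅) to √((k − 1)/χ²₀.₀₂₅), with k − 1 degrees of freedom.

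| k | Relative SE | 95% multipliers |
|---|---|---|
| 1 | undefined (0 df) | – |
| 4 | 1/√6 = 0.408 | 0.57 to 3.73 |
| 7 | 1/√12 = 0.289 | 0.64 to 2.20 |
| 10 | 1/√18 = 0.236 | 0.69 to 1.83 |
| 90 | 1/√178 = 0.075 | 0.87 to 1.17 |

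One baseline survey gives a mood level but no stability. Ratings over the existing run-in make a baseline estimable, though far less precisely than the treated period.

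**The case against.** **The start date may be ambiguous rather than late.** In Table 3 the glucose monitor has only visit marks, yet it is worn for days, so a baseline mark can stand for a series. The ring shares the undated Daily column with the mood survey and is worn before treatment. The baseline visit also refers to Table 1, which lists the daily survey. This stands in part: Table 3 does not exclude run-in ratings. But the pre-intervention wear of both devices is stated expressly in the text, whereas the only start the text gives for mood ratings is the intervention period. The full protocol might settle it; the article does not.

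**Other contrasts remain.** Early versus late intervention, and intervention versus follow-up, can still be estimated. That is true, but early intervention days are already treated and follow-up days come after about 90 days of exposure. Neither is an untreated baseline.

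**Stronger readings a reader might infer.**

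- *That mood has no baseline at all.* The documents do not support this: Table 3 schedules a baseline mood survey as well as YMRS, BDI and PHQ-9.
- *That no participant will have a usable stability baseline.* This treats one reading of an ambiguous schedule as settled.
- *That Exploratory Hypothesis 1 fails.* It is a correlation that specifies neither baseline nor change, and the post-intervention scan can be paired with late-intervention and follow-up ratings.
- *That Exploratory Hypothesis 3 is lost.* Its functioning half has baseline, mid and post measurements.

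**Conclusion.** The point holds in limited form. The article states no pre-intervention daily series for mood stability. As written, change from pre-intervention in that outcome, which is part of Exploratory Hypothesis 3 and would be among the Section 4 pre/post differences, has no untreated reference. The baseline scan has no concurrent daily mood data for Exploratory Hypothesis 1.

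The primary fMRI outcome, the changes in YMRS, BDI, PHQ-9 and the functioning scales, and Exploratory Hypothesis 1 at the post-intervention scan are untouched. Because only exploratory analyses are affected, this should be fixed but does not threaten the trial's main aim.

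The conclusion rests on the Section 3.3 text governing where Table 3 is silent. The precision figures rest further on a within-person SD and on independent normal days; independence is a strong assumption for daily mood in an episodic disorder.

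**What to change.** Start the CareEvolution daily survey on the first day of the existing 7 (±3)-day run-in, alongside the glucose monitor and ring. Name those ratings as the mood-stability baseline, and align the procedures text in Section 3.3 with Table 3 so that both give the same start.

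The cost is a short protocol edit, earlier activation of an app already in use, and about 4 to 10 extra brief ratings per participant. The limit is precision: a 4-day run-in gives a relative standard error of about 41% per person, so individual baselines should be read cautiously.

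If run-in ratings are not to be collected, reword Exploratory Hypothesis 3 so that it claims no change from baseline in mood stability. If the full protocol already starts the survey in the run-in, only the clarification is needed.
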